### Sample size

We estimated a sample size of 24 participants per group, yielding a total sample size of 48 participants. However, because of the crossover design of this trial we will only need a total of 24 participants, as each of them will participate in both interventional arms. We used the following parameters for the sample size calculation: an alpha value of 0.05, power of 80%, two different intervention groups with a crossover design, and a minimal clinically important difference between the groups compared of 40% in the frequency of hypoglycemic events. Considering also a 15% dropout rate during the clinical trial, we obtained a required sample size of 28 participants for each group.

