### Primary outcome

We will compare the percentage of participants with one or more confirmed hypoglycemic episodes (≤60 mg · dL^-1^) in the next 24 h following the assessment session. Other safety-related end points include changes in the mean and variability of 24-h plasma glucose based on CGM. Percentages of participants with hypoglycemic events will be calculated as categorized by the ADA^70^ and will be analyzed during the day (daytime; 6:00 a.m. to 11:59 p.m.), during the night (nocturnal; 12:00 midnight to 05:59 a.m.), and any time of day or night (24 h).

Precisely, hypoglycemic categories will include the following: (1) any hypoglycemia (events whether confirmed by self-measurement or not and whether symptomatic or asymptomatic); (2) documented symptomatic hypoglycemia (symptomatic events with plasma glucose ≤60 mg · dL^-1^); (3) asymptomatic hypoglycemia (events confirmed by plasma glucose ≤60 mg · dL^-1^ but without symptoms); and (4) severe hypoglycemia (events requiring assistance by another person to administer carbohydrate, glucagon, or other therapy). Confirmed or severe hypoglycemia will include documented symptomatic or asymptomatic events together with severe events.

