**Fig. 4 Fig4:**

Schematic representation of the order of soccer assessments according to the protocol. *LIST-P* Loughborough Intermittent Shuttle Test Prescribed and Self-Paced, *LSST* Loughborough Soccer Shooting Test, *LSPT* Loughborough Soccer Passing Test

Additionally, as exploratory outcomes we will also assess cognitive functions, given that hypoglycemia has long been thought to influence these functions in people with diabetes mellitus. A field study of school-aged children with T1D has shown that low blood glucose level impairs patients’ sports performance and produces detrimental cognitive effects, as measured by math test performance [8]. In this sense we set forth to evaluate, as a secondary outcome, the effect of the 4-step method on the cognitive performance of the subjects, related also to the frequency of hypoglycemic events and to the performance in soccer indexed by the tests described. We hypothesize that besides showing an adequate safety profile (same or reduced number of hypoglycemic events), the 4-step method will also allow the subjects to achieve a better performance both in soccer and in cognitive testing (see Fig. 5 for a summary of the planned study interventions and assessments).

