In the event that the data do not follow the normal distribution even after the log-transformation, we will conduct non-parametric analyses using the Wilcoxon-Mann-Whitney test and calculate Spearman correlation coefficients for the comparison between the two groups of the performance scores in soccer and cognitive tests, and for the linear correlation analysis, respectively. A *p* value <0.05 will be considered significant for the comparison of the scores.

Additionally, we will conduct exploratory analyses by modeling the performance scores in soccer evaluations adjusted by age, years since T1D diagnosis, HbA1c level, weekly physical activity hours and Stroop test scores using linear multiple regression. A *p* value <0.10 will be considered significant to introduce a variable into the multivariate regression model. The number of hypoglycemic events and the percentage of other adverse effects listed previously will also be compared among groups using Student’s *t* test and the Fisher exact test, respectively. All of the statistical analysis will be done using Stata software (StataCorp LP® 13.1).

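### The 24 participants match an unpaired calculation at mid-range rates, and at those rates a paired test secures 80% power only with some within-person correlation; the effect, endpoint and total also need restating

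*Protocol article*

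**What the plan says.** All of the following is in the protocol article.

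- **Sample size, design inputs:** "an alpha value of 0.05, power of 80%, two different intervention groups with a crossover design".
- **Sample size, effect:** "a minimal clinically important difference between the groups compared of 40% in the frequency of hypoglycemic events". No control rate is given, and the text does not say whether 40% means percentage points or a relative reduction.
- **Sample size, first result:** "We estimated a sample size of 24 participants per group, yielding a total sample size of 48 participants". The next sentence reduces this: "because of the crossover design of this trial we will only need a total of 24 participants", the reason given being that everyone receives both interventions.
- **Sample size, after dropout:** "Considering also a 15% dropout rate during the clinical trial, we obtained a required sample size of 28 participants for each group".
- **Trial status:** the target is 28 patients, with recruitment pending.
- **Primary outcome:** "We will compare the percentage of participants with one or more confirmed hypoglycemic episodes", at a threshold of 60 mg/dL or below, in the 24 hours after the session. This is a yes/no result observed twice in each person.
- **Statistical methods:** the number of hypoglycemic events and the percentage of other adverse effects "will also be compared among groups using Student’s *t* test and the Fisher exact test, respectively". No test is assigned outright to the primary percentage, and no paired test for binary data is named.

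**The concern.** The section calculates a number per group for two separate groups, then counts the same people twice because the design is a crossover. That step counts heads. The power of a paired binary comparison depends on the discordant pairs, and so on both event rates and the within-person correlation, and none of these is given.

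Three further points make the paragraph hard to use. The effect is set on the frequency of events, while the primary outcome is the share of participants with at least one event. The final figure is given per group in one section and as a total in another. The dropout allowance does not quite preserve the 24 completers it is meant to protect.

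At stake is whether the trial can claim 80% power for its primary safety comparison. A reader cannot tell from the text whether power is near 80% or far below it.

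**Working it through.** **Inputs.** From Sample size: alpha 0.05, power 80%, difference 40%, n = 24, dropout 15%. Assumed because not stated: two-sided testing, the control rate, and the within-person correlation (phi).

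**1. Reproducing 24.** The uncorrected two-proportion formula with pooled variance is

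n per group = [1.960·√(2·p̄(1−p̄)) + 0.842·√(p1(1−p1) + p2(1−p2))]² / (p1−p2)²

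At 70% versus 30%: [1.960·√0.50 + 0.842·√0.42]² / 0.16 = (1.386 + 0.545)² / 0.16 = 23.3, rounded up to 24.

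| Rates | n per group | Rounded up |
|---|---|---|
| 65 vs 25, or 75 vs 35 | 23.1 | 24 |
| 70 vs 30 | 23.3 | 24 |
| 60 vs 20 | 22.3 | 23 |
| 50 vs 10 | 19.4 | 20 |
| 90 vs 54 (relative 40%) | 23.2 | 24 |
| 70 vs 42 (relative 40%) | 48.1 | 49 |
| 50 vs 30 (relative 40%) | 93.0 | 93 |

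So 24 is a standard result for an absolute 40-point difference with a control rate of about 65% to 75%. A relative 40% returns it only near 90% versus 54%.

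**2. Power at those rates.** Power comes from full enumeration. For McNemar at 70/30, phi = 0 gives discordant probabilities 0.7 × 0.7 = 0.49 and 0.3 × 0.3 = 0.09. At phi = 0.2 the covariance is 0.2 × 0.21 = 0.042, so these become 0.448 and 0.048.

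| 70 vs 30 | phi 0 | phi 0.2 |
|---|---|---|
| Fisher exact, 24 in each condition | 75% | 77% (79% at phi 0.3) |
| Exact McNemar, 24 pairs | 70% | 80% |
| Mid-p McNemar, 24 pairs | 78% | 87% |
| Exact McNemar, 23 pairs | 68% | 78% |

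At 70/30 without correlation, either exact test needs 29 to reach 80%.

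**3. Power at other absolute rates, n = 24, phi = 0.**

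| Rates | Fisher exact | Exact McNemar |
|---|---|---|
| 60 vs 20 | 76% | 72% |
| 55 vs 15 | 79% | 75% |
| 50 vs 10, or 90 vs 50 | 83% | 80% |
| 45 vs 5, or 95 vs 55 | 90% | 87% |

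**4. If 40% is relative, n = 24, phi = 0.** Exact McNemar gives 19% (50 vs 30), 37% (70 vs 42), 51% (80 vs 48), 71% (90 vs 54) and 83% (95 vs 57).

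**5. Dropout.** 28 × 0.85 = 23.8, just under 24. Dividing by the retained fraction gives 24/0.85 = 28.2, or 29. Multiplying gives 24 × 1.15 = 27.6, or 28. The article does not show which was done.

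**6. The total.** Sample size gives 28 for each group and Trial status gives 28 patients. Read literally as separate groups, the first would be 2 × 28 = 56.

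**The case against.** The strongest reply is that power cannot be called too low when the rates that determine it are not given. That is right, and it limits the point. A reader might infer that 80% power is simply not delivered, or that 24 arises only from 70% versus 30%. Neither follows. The 70/30 case is the least favourable for a 40-point difference, the neighbouring rates also return 24, and control rates of about 50% or below, or 90% or above, give about 80% or more. Even at 70/30, the mid-p test comes within two points of 80% at phi = 0. Modest positive correlation, which is plausible for two sessions in one person, closes the gap.

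Fisher's test cannot be called the planned primary test either. Statistical methods attaches it to other adverse effects, so its use for the primary percentage is an inference. Severe underpowering does not follow from a relative reading alone, since it also depends on the control rate. An absolute reading fits the stated 24 more readily.

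It can also be said that a condensed article may leave the correlation and the test to a fuller document. Their absence alone would not be a finding. What remains is that the printed paragraph carries an unpaired number into a paired design, with an effect of undefined scale on a different quantity from the primary outcome.

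The per-group wording is probably loose, because each arm contains the same people, and one participant in the dropout step is small. Both are still easy to correct.

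Finally, a hypothesis just before Fig. 5 describes an adequate safety profile as "same or reduced number of hypoglycemic events". A reader might infer that a non-significant result will be read as equivalence. The article sets no such decision rule, so this is not part of the point.

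**Conclusion.** The point holds in a conditional form, at moderate severity. The 24 is a correct unpaired calculation for a 40-point difference at control rates of about 65% to 75%. At 70/30 with 24 participants, the stated 80% is not secured. Power is about 75% with Fisher (77% to 79% on paired data at phi 0.2 to 0.3), and about 70% with exact McNemar at phi = 0, rising to 80% at phi of about 0.2. With 23 completers, exact McNemar gives 68% and 78%. More extreme absolute rates reach about 80% or more. A relative 40% at control rates of 50% to 70% would leave about 19% to 37% with exact McNemar at phi = 0.

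These figures assume two-sided testing at 0.05, and the rates and correlations shown are assumptions. Two points do not depend on them: the effect is stated on a different quantity from the primary outcome, and the per-group 28 must be reconciled with the total of 28.

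**What to change.** Rewrite the Sample size paragraph and add one sentence to Statistical methods:

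1. State the effect as 40 percentage points in the percentage of participants with at least one confirmed episode, and give the assumed rate under each intervention.
2. Name McNemar's test, and whether exact or mid-p, for both the calculation and the primary comparison.
3. State the assumed within-person correlation and the resulting power at 23 to 24 completers. For exact McNemar at 70% versus 30% this is 68% to 70% at phi = 0 and 78% to 80% at phi = 0.2.
4. Replace the per-group 28 with 28 participants in total, matching Trial status. Keeping 28 is acceptable if power is stated at 23 completers as well as 24.

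The cost is rewording, with no change in enrolment. The stated power may become somewhat less favourable. Trial status lists recruitment as pending, so the change can be made before any data exist.

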### Randomization

We will use block-stratified randomization, with random 2 − 4 sized blocks and stratified by gender. A statistician not related to the protocol will generate the randomization list using a web-based method (http://www.randomizer.org) that will randomize the order of the interventions assigned. We will then have sequentially numbered, sealed, opaque envelopes with the allocations inside, in order to maintain allocation concealment throughout the randomization process. After the patient is consented and enrolled in the trial, an un-blinded endocrinologist (also in charge of the educational sessions) will open the assigned envelope, allocate the subject to the group presented and coordinate with the pharmacy and nutritional department for the preparation of the insulin and dietary modifications needed with respect to the interventional arm assigned.

As mentioned before, the main objective that guides this exercise protocol is not to demonstrate differences in the response of subjects with T1D to different exercise modalities, such as continuous versus intermittent exercise. On the contrary, we want to evaluate the impact, in terms of safety and performance, of a protocol that sets forth insulin dosage along with carbohydrate intake diet modifications, compared with usual-care recommendations stated by guidelines for standard of care. This being said, it is worth adding that other trials [2, 10, 11] have evaluated the response of subjects to the 4-step method, so we would be increasing knowledge of this particular intervention.

### Blinding

In this trial, both participants and assessors will be blinded. Likewise, the statistical team in charge of data analysis will not know the real allocation of the participants and will handle data as “intervention A” and “intervention B”. In order to assure adequate blinding of the participants, we developed a sham 4-step method control intervention whereby we will administer the usual ADA recommendations masked in a 4-step method scheme similar to the real intervention (see Table 2). In this way, participants will feel that both are experimental trials even though they will be receiving different insulin and dietary regimens. Furthermore, all the assessors in charge of applying the soccer and cognitive evaluations will also be blinded until the end of the trial. We will have an un-blinded group of physicians that will be in charge of assigning patients to their allocations, applying and explaining the therapeutic and dietary modifications for each intervention, and monitoring glucose parameters and dietary or physical activity related adverse effects during the trial. Finally, before switching groups and at the end of the trial, we will assess the efficacy of blinding using a questionnaire that will be administered to the participants.

### Data collection

We will assemble a folder for each participant containing the data collection sheet that will include information acquired at the first visit on demographic data, clinical history, basal laboratory results, and the simulated soccer tests and cognitive function evaluation scores.

Blood glucose levels will be documented with glucometers. Given the simultaneous participation of several participants with T1D in the training sessions, five of these devices will be available for the research team in case of an accident or malfunction of an individual system. Glucometers *Accu-Check Nano* will be calibrated using the Accu-Check Smartview Glucose Control Solution every time and immediately before delivering them to each subject. Using this system, we will be able to identify if the glucometer is giving a correct value within a range previously established for the protocol. In the given case that the result is not within the desired range, then the device will no longer be used in the trial At the end of the 24-h follow up, the investigation team will check the recording after the training sessions and compare it with the finger stick results.

### Statistical methods

In order to evaluate glucose control, we will also compare the two groups, using either Student’s paired *t* test or the Wilcoxon-Mann-Whitney test, in terms of CGM parameters that include: 24-h mean glucose levels, SD of 24-h glucose levels, area under the curve for 24-h glucose, mean amplitude of glycemic excursions, number of episodes of hypoglycemia (<60 mg · dL^-1^), time in hypoglycemia (<60 mg · dL^-1^) during a 24-h period, time in hyperglycemia (>180 mg · dL^-1^) during a 24-h period, and range of postprandial glucose increase. The range of glucose increase (from pre-meal to post-prandial peak levels) after breakfast, lunch, and dinner, will also be compared between the interventional groups, using either repeated measures analysis of variance (ANOVA) or the Kruskal-Wallis test, depending on the normality of the data distribution.

We will assess for data from the LIST-P, LSPT, and LSST, and the Stroop, DVT, DBT, and RVIP test scores obtained for each assessment session, for normality of distribution using histogram analysis, the Shapiro-Wilk test and the Kolmogorov-Smirnov test. We will use a logarithmic transformation for the correction of non-normal data and will subsequently test for the differences between groups using Student’s paired *t* test. In order to assess if the order of the intervention modified the performance of individual participants, we will calculate the difference of the scores obtained between the two types of interventions (real intervention minus sham 4-step method) and then we will define an intervention indicator variable that will take the value of 1 if the subject started with the real 4-step method, and 0 if the subject started with the sham 4-step method. We will then fit a linear regression model with the difference calculated as the response variable and the intervention indicator along with other relevant covariates (age, gender, BMI) as the independent variables. Moreover we will test for time effect over the performance of the participants in a time-varying regression model. Additionally, Pearson correlation coefficients will be calculated between each of the scores and the pre-exercise blood glucose level, searching for linear correlation between blood glucose values and the LIST-P, LSPT, LSST, and Stroop test scores.

In the event that the data do not follow the normal distribution even after the log-transformation, we will conduct non-parametric analyses using the Wilcoxon-Mann-Whitney test and calculate Spearman correlation coefficients for the comparison between the two groups of the performance scores in soccer and cognitive tests, and for the linear correlation analysis, respectively. A *p* value <0.05 will be considered significant for the comparison of the scores.

Additionally, we will conduct exploratory analyses by modeling the performance scores in soccer evaluations adjusted by age, years since T1D diagnosis, HbA1c level, weekly physical activity hours and Stroop test scores using linear multiple regression. A *p* value <0.10 will be considered significant to introduce a variable into the multivariate regression model. The number of hypoglycemic events and the percentage of other adverse effects listed previously will also be compared among groups using Student’s *t* test and the Fisher exact test, respectively. All of the statistical analysis will be done using Stata software (StataCorp LP® 13.1).

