#### Active intervention: real 4-step method

Participants will come to the laboratory at 7:00 a.m. and we will first obtain a resting, fasted venous blood sample (via venipuncture) for the laboratory evaluations previously listed. The iPro2 Professional continuous glucose monitor (CGM) with Enlite sensor (Medtronic, MN, USA) will be installed at that time. Participants will then consume a standardized cereal-based breakfast meal (sugar-coated corn flakes, peaches, and semi-skimmed milk; 1.3 g carbohydrate · kg^-1^ body mass). At 1:00 p.m. participants will consume a standardized pasta-based lunch meal (pasta, tomato-based sauce, cheddar cheese, olive oil; 1.3 g carbohydrate · kg^-1^ body mass). Between the morning and evening visits, participants will record their self-measured glucose control every 2 h.

At 5:00 p.m. participants will arrive for the evening training session. Before starting this session, they will self-administer a 50% reduced pre-meal rapid-acting insulin dose into the abdomen (the injection site will be at the mid-point between the iliac crest and the navel). Immediately after receiving this insulin dose, participants will consume a pre-exercise carbohydrate bolus (sugar-coated corn flakes, peaches and semi-skimmed milk; 1.0 g carbohydrate · kg^-1^ body mass). Following this bolus, participants will remain rested for 60 min, at which point a finger stick sample for glucose testing will be drawn immediately before starting with the training sessions.

At 60 min post-exercise, participants will self-administer a pre-meal rapid-acting insulin dose reduced by 50%, into the abdominal site contralateral to the previously administered pre-exercise rapid-acting insulin injection. After receiving this insulin dose, participants will consume a carbohydrate-based meal (basmati rice, tomato-based sauce, turkey breast, and an isomaltulose orange flavored drink (10% solution); 1.0 g carbohydrate · kg^-1^ body mass) designed to elicit a low GI (GI = 37) response [2].

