#### Control intervention: usual recommendations (sham 4-step method)

Recently, ADA published a position statement about physical activity and diabetes [16]. This statement explained how the variable glycemic responses observed in association with physical activity makes it very difficult to provide uniform recommendations for both the management of food intake and the insulin dosing regimen. Nonetheless, several instructions in this document are intended to help prevent hypoglycemia. To prevent low blood glucose level during prolonged (>30 min), predominantly aerobic exercise, additional carbohydrate intake and/or reductions in the insulin dose are typically required [12–16]. In addition to the changes in insulin regimen and carbohydrate intake, a brief (10 s) maximal intensity sprint could be performed before or after the exercise session, as suggested in the ADA guidelines, to prevent exercise-induced hypoglycemia [12]. The position statement also recommends adjusting daily basal insulin dose with reduced prandial bolus insulin and low-GI carbohydrate feeding following evening exercise for those on multiple daily injections [12]. Finally, inclusion of a bedtime snack, overnight glucose checks, or alarms and automatic pump suspension may also be warranted [16].

Patients allocated to the control group, or sham 4-step Method, will receive current usual recommendations as stated by the ADA [16], but following the scheme established with the real 4-step method (see Table 2 for the comparison for both interventions). Prior to exercise, the CGM will be installed at 7:00 a.m., and they will receive their meals in the same amount and frequency as in the real 4-step method, consisting of a breakfast at 8:00 a.m., lunch at 1:00 p.m. and pre-exercise meal at 5:00 p.m. All of the three meals will have the same caloric content as in the real intervention, and there will be no insulin modification for the first two meals. Assuming that they will be performing moderately intense physical activity later in the day, for up to 60 minutes, this group will receive a rapid-acting insulin dose that will be 75% of their usual dose concomitantly with the 5:00 p.m. meal prior to the onset of physical activity.

**Table 2 Tab2:** Scheme comparison of interventions delivered in the real and sham 4-step methods

Time		Real 4-step method	Control (sham) 4-step method
8:00 a.m.	Breakfast	Standardized cereal-based breakfast	Standardized cereal-based breakfast

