## Discussion

During clinical trials the 4-step method has been demonstrated to optimize blood glucose levels during and after exercise by making mealtime adjustments to both rapid-acting and basal insulin and to pre-exercise and post-exercise carbohydrate composition [2]. The first step of this method protects individuals with T1D from concomitant and early exercise-induced hypoglycemia [6], the second step prevents a rapid rise in blood glucose because of an overcorrection with food using a low-GI carbohydrate meal [7], and the third and fourth steps are intended to guard against late-onset exercise-induced hypoglycemia after physical activity [2, 11].

Intermittent exercise, such as soccer, is more demanding on the body than continuous exercise of the same average intensity [21]. The 4-step method has never been tested in a clinical trial setting for the evaluation of intermittent forms of exercise, such as soccer.

We expect that this protocol will stimulate the development and execution of clinical trials to evaluate dietary and pharmacological interventions that will help patients with T1D engage in physical activity, reduce the risk of glycemic derangements while conducting exercise, and at the same time obtain the best physical and cognitive performance possible.

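### The dinner glucose rise is measured from a pre-meal value the regimens have already changed, so a smaller rise may only reflect a higher start

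*Protocol article*

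**What the plan says.** In the protocol article, Statistical methods, the list of CGM parameters compared by paired t test or Wilcoxon-Mann-Whitney test ends with "and range of postprandial glucose increase". The next sentence defines the measure per meal: "The range of glucose increase (from pre-meal to post-prandial peak levels) after breakfast, lunch, and dinner, will also be compared" between the arms, "using either repeated measures analysis of variance (ANOVA) or the Kruskal-Wallis test, depending on the normality of the data distribution". It names neither a per-meal comparison of pre-meal glucose nor one of the absolute peak.

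The insulin given before dinner differs by arm. In the real 4-step arm, at 5:00 p.m., "they will self-administer a 50% reduced pre-meal rapid-acting insulin dose into the abdomen". In the control arm the text says "this group will receive a rapid-acting insulin dose that will be 75% of their usual dose concomitantly with the 5:00 p.m. meal", while Table 2 lists a 75% reduction for the same dose. The post-exercise meal follows; Table 2 calls it dinner in the control column.

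After dinner the arms also differ in dinner insulin, in the glycemic index of dinner and snack, and in basal insulin. The breakfast dose next morning is full in both arms. Breakfast and lunch on the exercise day carry no insulin change in either arm.

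**The concern.** A rise from a starting value is a clean comparison of meal handling when the starting value is a true baseline. Before dinner it is not. The arms have by then had different rapid-acting doses, and the Discussion states what the first step is for: "The first step of this method protects individuals with T1D from concomitant and early exercise-induced hypoglycemia". The article therefore expects that step to act on glucose in the hours just before dinner.

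The Discussion also credits the second step, the low-glycemic-index meal, with preventing a rapid rise. A smaller dinner rise would naturally be quoted as support for step two, although it could come from step one having changed the start. The arm with the higher post-exercise glucose gains the advantage, even if its peak is equal or higher.

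The rank tests named for this outcome add a second weakness. Kruskal-Wallis and Wilcoxon-Mann-Whitney treat the arms as independent groups, but every participant receives both regimens.

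**Working it through.** The article states no figure for this outcome, so there is none to reproduce.

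**1. Which meals start after the regimens diverge**

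- Exercise-day breakfast and lunch: same meals, insulin unchanged in both arms. Not affected.
- Dinner: preceded by the 5:00 p.m. dose. On the text, the arms receive 50% and 75% of the usual dose. On Table 2, they receive 50% and 100% − 75% = 25%. Either way they differ by 25 percentage points of the usual dose, but in opposite directions. Affected.
- Next-morning breakfast: preceded by different dinner insulin, different glycemic index of dinner and snack, and a 20% versus no basal reduction. It lies within the CGM window. Affected, if this is the breakfast meant; Statistical methods does not say.

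**2. Algebra**

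Difference in rise = difference in peak − difference in pre-meal glucose.

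Let the regimen shift pre-meal glucose by D, let a fraction r of the shift carry through to the peak, and let m be the effect of the meal itself on the peak. Then the difference in peak is rD + m, and

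difference in rise = rD + m − D = m − (1 − r)D.

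The term −(1 − r)D is present whatever the meal does. It vanishes only if r = 1.

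Example with assumed values: arm A goes from 120 to 220 mg/dL, a rise of 100. Arm B goes from 160 to 230, a rise of 70. The difference in rise is 10 − 40 = −30 mg/dL, so B scores better although both its start and its peak are higher.

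**3. Size, under stated assumptions**

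Inputs: n = 24 from Sample size; D, r and the SD of the paired difference in rise are assumptions. The test is a paired t for one meal, two-sided 0.05, with no meal effect (m = 0). The noncentrality is (1 − r)D/SD × √24.

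The critical difference is 2.069 × SD/√24: 16.9 mg/dL for SD 40 and 25.3 mg/dL for SD 60.

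Chance of p<0.05 from the starting shift alone:

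| D (mg/dL) | SD (mg/dL) | r = 0 | r = 0.5 | r = 1 |
|---|---|---|---|---|
| 10 | 40 | 22% | 9% | 5% |
| 10 | 60 | 12% | 7% | 5% |
| 20 | 40 | 65% | 22% | 5% |
| 20 | 60 | 35% | 12% | 5% |
| 40 | 40 | 99.7% | 65% | 5% |
| 40 | 60 | 88% | 35% | 5% |

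With the inflated 28 participants, D = 20 and SD 40 give 72% at r = 0 and 25% at r = 0.5.

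**4. If the rise is averaged over three meals**

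If only dinner is affected, a shift of 20 mg/dL becomes 20/3 = 6.7 mg/dL. At r = 0 the chance is then about 12% if the averaged difference has SD 40, and about 27% if its SD is 40/√3 = 23.1.

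**The case against.** The rise is a legitimate quantity. It describes how far glucose climbs after a meal, which is what the Discussion says the second step should limit. The article does not make it the sole measure of postprandial control, nor does it say that a smaller rise shows benefit whatever the level. This stands, and it is why the rise need not be dropped.

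Level is also compared elsewhere: 24-h mean, 24-h area under the curve and time above 180 mg/dL are in the same list, and an arm that starts and peaks higher would tend to show it there. This stands in part. None of these is per meal, so none shows whether a smaller dinner rise comes from the meal or from the start.

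Absolute peak has a limitation of its own: when r exceeds 0, it too is moved by the pre-meal level. That is a reason to show pre-meal glucose, absolute post-meal glucose and rise together, rather than to replace one with another.

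The two sentences on testing can be read as an overall comparison plus a per-meal analysis, so they need not contradict each other. The independent-group rank tests are still wrong for paired data on either reading.

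A reader might also infer that all three meals are affected. Two of the three are clean if the exercise-day meals are meant, which fits the order in Table 2.

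**Conclusion.** The point holds for dinner, and for the next-morning breakfast only if that is the breakfast intended. The pre-meal value there is a regimen effect, and subtracting it can turn a higher start into an apparently better result.

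Its size cannot be fixed from the article. For a 20 mg/dL shift and 24 participants, the chance of a significant difference from the start alone runs from 5% to 65% with SD 40, and from 5% to 35% with SD 60, depending on how much of the shift reaches the peak. A reader might take the upper figures as the expected error rate. The documents do not support that: those figures assume that none of the shift carries through, and the shift and SD are themselves assumptions.

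A reader might also infer that the measure favours the real 4-step arm. The direction before dinner is open, because the control text and Table 2 give opposite orderings of the 5:00 p.m. doses; those two places must be reconciled. Before the next-morning breakfast the insulin reductions would suggest a higher start in the real arm, but the glycemic index of dinner and snack differs too.

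The primary outcome, confirmed hypoglycemia, is not touched. Minor priority.

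**What to change.** In Statistical methods:

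- State which day's breakfast and lunch are meant.
- For dinner, and for the next-morning breakfast if used, also compare absolute post-meal CGM glucose between regimens: the peak, or the mean over a fixed time after the meal.
- Report pre-meal glucose by regimen beside it. Do not adjust for it, since it lies on the path of the regimen's effect.
- State that a smaller rise will not be read as better postprandial control unless absolute post-meal glucose is also no higher.
- Name one within-participant test for this outcome, the paired t test or the Wilcoxon signed-rank test if non-normal, in place of Kruskal-Wallis and Wilcoxon-Mann-Whitney.

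The cost is a few sentences and one extra summary from the CGM already worn, with no new data. The price is a more cautious reading of the rise. Recruitment is listed as pending under Trial status, so the wording can be settled before data are seen.
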